**Fig. 3 Fig3:**
[figure not shown]
CPIPE study design

### Study population

The study population includes providers and women who give birth in the study facilities. Providers are the recipients of the intervention as well as potential beneficiaries. All healthcare workers (including nurses, midwifes, doctors, clinical/medical officers, and support staff) who provide MCH services (including antenatal, intrapartum, and postnatal care) in study facilities will be eligible for the intervention. Including all providers in a facility will facilitate an enabling facility culture, across all cadres. Women who receive care in the study facilities are the anticipated beneficiaries of the intervention; we will obtain data on the primary outcomes among women. Study participants will be women who gave birth in the facility in the 12 weeks preceding data collection. Other eligibility criteria are shown in Table 1.

**Table 1 Tab1:** Eligibility criteria

**Eligibility criteria for providers**
1. Working in the maternal health units of study facilities for at least 6 months at the time of data collection
2. Capable and willing to provide informed consent
3. Able and committed to attending the intervention training and follow up activities
4. Age 18 or above
**Exclusion criteria for providers**
Intend to leave within the study facility/catchment during the 6-month intervention period
Eligibility criteria for women
1. Gave birth at the study facilities
2. Gave birth within the 12 weeks preceding the data collection
3. Capable and willing to provide informed consent
4. Age 15 or above, with individuals aged 15-17 meeting the criteria for emancipated minors

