#### Sample size

Participants include 400 providers (*N* = 400) followed longitudinally and *N* = 6000 women participating in multiple cross-sectional surveys- baseline (*N* = 2000), midline (*N* = 2000), and endline (*N* = 2000)- across both countries: i.e., 200 providers followed longitudinally, and 3000 women interviewed once across three time points (*N* = 1000 at each time-point) from both intervention and control facilities, in each country. We will then conduct IDIs with a subset of providers (N = ∼ 40), facility leaders (N = ∼ 40), and mothers (N = ∼ 40) to explore pathways to intervention outcomes. Power analysis for sample size justification is described in the analysis section.

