#### Recruitment

The study will first be introduced to the county/region, sub-county/district, and facility leadership, who will inform all providers who work in MCH units in the study facilities. The study’s field team will then approach individual providers to provide additional information and obtain written informed consent. Only providers who provide individual informed consent will be enrolled. They will be made aware that participation in the study is voluntary and will not affect their positions in any way. Providers in the selected facilities will be recruited by the field team and consented at the beginning of the study and then followed longitudinally for the three rounds of data collection. Women will be recruited at health facilities following discharge from the facilities and after postnatal care and in the immediate communities served by the study facilities. They will first be identified with the help of healthcare providers, community health volunteers, and a review of facility birth registers at the study sites. The study team will then screen them for eligibility, provide information about the study, and obtain individual informed consent if interested. Only women who provide written consent will be interviewed either at the facility, at their homes, or at a preferred location. Following surveys, all participants will be asked if they are willing to be contacted for follow-up IDIs; a subset of those who consent will be re-contacted for the IDIs. Participants for IDIs will be purposively sampled balancing for age, time/weeks since birth, and post-natal care attendance, to represent the range of experiences. All women will be consented prior to IDIs.

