#### Aim 3: Outcomes to Assess the effect of the CPIPE intervention on distal outcomes in our conceptual framework (Fig. 2) include

receipt of timely postnatal care, breastfeeding initiation and exclusivity, postpartum mental well-being, and post-delivery neonatal complications, which we have shown are associated with PCMC [29, 30]. These will be measured using questions on the timing of breastfeeding onset and current breastfeeding practices, the Edinburgh postnatal depression scale [68], and other questions on postpartum and newborn health in the women’s survey. We will also collect facility-level data on coverage indicators and maternal and neonatal morbidity and mortality from facility records. All study outcomes and sample measures are shown in Table 2. As part of all surveys, we will collect data on various covariates shown in Table 2.

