While facility data will be limited to *N* = 40 clinics, inferential analyses will be performed with *N* = 2000 women on distal outcomes. We focus on the key outcome of receipt of timely post-natal care. We hypothesize that among mothers giving birth in the study facilities, mothers who received care in the *CPIPE* intervention group will be more likely to receive postnatal care within 48 h than mothers in the control group at 6 months (H3a) and 12 months (H3b) after baseline. To test H3a and H3b, we will fit two-level generalized linear mixed models (GLMM) to the binary timely postnatal care variable collected at 6 months and at 12 months. Each model will include a fixed effect for study arm and random intercepts for facilities for clustering of women within health facilities. Because we will compare *CPIPE* to control at 6 months and at 12 months, α will be set at.05/2 = 0.025 for each comparison. We will use the same GLMM approach to test the effects of *CPIPE* on other distal outcomes. Additional secondary exploratory analyses for Aim 3 will explore whether the PCMC scores mediate the relationship between *CPIPE* intervention exposure and receipt of timely post-natal care. As in specific Aim 2, we will perform mediation analyses using SEM and causal mediation methods [79]. Sex as a Biological Variable is not applicable because all care recipients will be biological females.

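### No minimum time since birth is set, so the 48-hour postnatal care outcome may be asked before its window has closed, and other time-dependent Aim 3 outcomes are compared without regard to interview day

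*Protocol article*

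**What the plan says.** The women's eligibility rule in Table 1 reads "Gave birth within the 12 weeks preceding the data collection", and the Study population section repeats it: "Study participants will be women who gave birth in the facility in the 12 weeks preceding data collection". Both set an upper limit, and neither sets a lower one.

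On where women are found, the Recruitment section says "Women will be recruited at health facilities following discharge from the facilities and after postnatal care", and adds the surrounding communities as a further source. On place, it says "Only women who provide written consent will be interviewed either at the facility, at their homes, or at a preferred location". It gives no rule on how long after birth the interview takes place.

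The Sample size section describes, for each country, "3000 women interviewed once across three time points". An answer that is incomplete on the day is therefore not updated by a second survey.

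Under Aim 3 of the Analysis plan, the hypothesis for the key distal outcome is that intervention mothers "will be more likely to receive postnatal care within 48 h than mothers in the control group at 6 months" (H3a), and again at 12 months (H3b). The model has a fixed effect for arm and a random intercept for facility, and the same approach is to be used for the other distal outcomes. Those are measured by "questions on the timing of breastfeeding onset and current breastfeeding practices, the Edinburgh postnatal depression scale" and by further questions on maternal and newborn health. In the text, time since birth is a balancing factor only when choosing women for the qualitative interviews.

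**The concern.** A 48-hour outcome can be read in full only once 48 hours have passed. A woman interviewed at the facility soon after discharge may not have reached that point. If she has had no postnatal check yet and is recorded as a no, a later check inside the window is lost.

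The other Aim 3 outcomes have a related difficulty. Exclusive breastfeeding tends to decline with infant age, neonatal complications accumulate, and a depression score at a few days does not describe the same state as one at ten weeks. With one interview anywhere in a 12-week window and no model term for its timing, part of the variation in these outcomes is simply variation in interview day.

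At stake are the sensitivity of H3a/H3b, which have their own alpha split and power calculation, and the interpretation of the other distal outcomes. If interview timing came to differ by arm, the arm comparison itself would be distorted.

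**Working it through.** **Inputs from the protocol.** 2000 women per time point and 40 facilities, so 50 per facility and 1000 per arm; power 0.80 (Aim 1 Power Analysis, whose approach Aim 3 follows); alpha 0.025 per comparison (Aim 3); ICC 0.039 and timely postnatal care of 24–81% (Aim 3 Power Analysis). Stated detectable differences: 8.3–10.7 percentage points.

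**Step 1: reproduce the plan's figure.** Design effect = 1 + (50 − 1) × 0.039 = 2.911. Effective number per arm = 1000 / 2.911 = 343.5. For two proportions with pooled variance under the null, power = Φ[(d − z·se0)/se1], with z = 2.2414 for two-sided 0.025. Solving for 80% power and an increase over the control rate:

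- From 24%: d = 10.69 points. Check: se0 = 0.0347 and se1 = 0.0345, so (0.1069 − 2.2414 × 0.0347)/0.0345 ≈ 0.84, and Φ(0.84) = 0.80.
- From 81%: d = 8.34 points.

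Both stated endpoints reproduce. The calculation treats the 48-hour outcome as fully observed in every woman.

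**Step 2: equal timing in both arms.** Let f be the share of women interviewed before 48 hours. Let u be the share, among those of them who will receive care inside the window, who have not yet received it at interview. If early interview is unrelated to eventual receipt and uncounted women are coded no, the observed rate is the true rate × (1 − k), with k = f × u. The documents give neither f nor u, so k is an assumption. A k of 0.05, for instance, is 10% interviewed early with half of the recipients among them uncounted. Starting from the unrounded contrasts of Step 1:

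| k | Contrast from 24% (points) | Power | Contrast from 81% (points) | Power |
|---|---|---|---|---|
| 0 | 10.7 | 80% | 8.3 | 80% |
| 0.025 | 10.4 | 78% | 8.1 | 73% |
| 0.05 | 10.2 | 77% | 7.9 | 66% |
| 0.10 | 9.6 | 73% | 7.5 | 53% |
| 0.20 | 8.6 | 66% | 6.7 | 36% |

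Example for k = 0.10 at the upper end: the rates become 0.81 × 0.9 = 0.729 and 0.8934 × 0.9 = 0.804, the difference is 0.0751, se0 = 0.0323 and se1 = 0.0322, so (0.0751 − 2.2414 × 0.0323)/0.0322 ≈ 0.085 and power ≈ 0.53. The loss is steeper at 81% because the contrast shrinks while the rates move towards 50%, where the variance is larger. At 24% the variance falls as well, which cushions the loss.

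**Step 3: timing that differs by arm.** With no true effect, the spurious difference is the true rate × the difference in k between arms. For a 10-point difference this is 0.24 × 0.10 = 2.4 points at the lower rate and 0.81 × 0.10 = 8.1 points at the upper. This is conditional: nothing in the protocol shows such a difference.

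**Step 4: the other outcomes.** No arithmetic is possible, because the protocol gives no age profile for them. The stated model has no term for time since birth, although the interview may fall anywhere in a 12-week range.

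**The case against.** The protocol gives neither discharge times nor an interview schedule, so a reader who infers that some women are in fact asked too early goes beyond the text. The rules permit it, and no more than that can be said. The recruitment sentence is also ambiguous. If discharge and postnatal care must both have happened, women recruited at facilities have already had postnatal care and the open-window problem goes away for them, although they are then selected on the outcome being tested. Nor does the protocol say that an unfinished window is coded as a no. Its plan to use maximum likelihood and multiple imputation would allow such women to be treated as incomplete. Table 2, where the covariates are listed, is not shown and may include time since birth. All of this stands, and it limits the point to what the stated rules allow.

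A reader might also infer bias between the arms. The window and the recruitment routes are the same in both, so the default consequence is dilution. There are routes by which timing could diverge: providers, who receive the intervention in one arm, help to identify women, and one recruitment point follows postnatal care, which the intervention is meant to increase. These make a difference possible but do not show one.

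A reader might assume that 10–20% are interviewed early and that 30% of those would still receive care in time, and so put the understatement at 3–6 points. That does not fit the lower end of the plan's range. At a 24% rate, unless early interviewees differ from other women, the loss is at most 0.10 × 24 = 2.4 to 0.20 × 24 = 4.8 points.

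The objection does not remove the gap. Analysis can add a covariate later, but it cannot recover a 48-hour answer that was taken too early, except by exclusion, imputation or another source. The Aim 3 model terms are also stated, and time since birth is not among them.

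**Conclusion.** The point holds as a modest correction to an exploratory aim. The stated rules allow an interview before the 48-hour window has closed, and they compare time-dependent outcomes over 0–12 weeks with no term for interview timing. With equal timing in both arms, the result is dilution and noise. For 5–10% of eventual recipients uncounted, power falls from 80% to about 77–73% at a 24% rate and 66–53% at an 81% rate. These figures rest on an assumed share, on coding uncounted women as no, and on early interview being unrelated to eventual receipt. Bias between arms would require differential timing and is not established.

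Two further readings are not supported. The stated 8.3–10.7 points are not wrong, since they reproduce. The primary PCMC comparison is not affected by this argument.

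**What to change.** For H3a/H3b, analyse only women interviewed at least 48 hours after birth, or take the 48-hour item from the postnatal register for those interviewed earlier. State the rule identically for both arms. Add days since birth at interview as a covariate in the models for breastfeeding exclusivity, depression score and neonatal complications. It can be derived from the date of birth that the eligibility check already requires. State as well whether recruitment at the facility requires discharge and postnatal care both to have occurred, because the covariate would not repair selection on postnatal care.

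The cost is small: one analysis rule, one covariate and, under the exclusion option, some women lost from an exploratory analysis. As an illustration, if 10% were excluded evenly, 45 per facility would remain. The design effect would be 1 + 44 × 0.039 = 2.716 and the effective number per arm 900 / 2.716 = 331.4 instead of 343.5. Detectable differences would grow by a factor of about √(343.5 / 331.4) = 1.018, to roughly 10.9 and 8.5 points. The PCMC sample and its analysis stay as they are.

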**Exclusion criteria for providers**
Too ill to participate or do not live within a feasible distance/location if interviews are scheduled to be conducted in the community

### Study procedures

#### Intervention

This will include participation in an initial 2-day training, followed by monthly refreshers to reinforce training content; peer support groups, each comprising 5–10 providers of similar cadre, who will meet for about 1–2 h every month; and in a mentorship program, in which mentor/mentee pairs are encouraged to meet once a month but will be primarily mentee-driven. Each facility will have two embedded champions, providers nominated by their peers who will lead activities at each site including facilitating refreshers and peer support groups. Leadership engagement will occur throughout the project through continuous interaction with leaders in the study sites and with a community advisory board which will meet quarterly to provide input on implementation and respond to provider concerns to address sources of stress.

#### Data collection

We will collect data at 3 time points in the intervention and control sites: baseline (T1) prior to the intervention start at each facility, midline 6 months post-baseline/intervention start (T2) to assess immediate impact, and endline 12 months after baseline (6 months post-intervention) (T3) to assess sustainability. Survey data will be collected utilizing Redcap programmed tablets. Process data will be collected throughout the study to assess intervention fidelity and implementation using study logs and Redcap. The provider cohort will be followed longitudinally for 12 months following baseline enrollment. The women’s sample will be multiple cross-sections, where data will be collected from 3 different groups of women at the 3 time points. We will use a mixed-methods approach. Quantitative data will be obtained from surveys followed by IDIs to qualitatively explore factors that may influence outcomes. We will also assess intervention fidelity through observations of intervention activities and a review of project logs [58, 59].

#### Sample size

Participants include 400 providers (*N* = 400) followed longitudinally and *N* = 6000 women participating in multiple cross-sectional surveys- baseline (*N* = 2000), midline (*N* = 2000), and endline (*N* = 2000)- across both countries: i.e., 200 providers followed longitudinally, and 3000 women interviewed once across three time points (*N* = 1000 at each time-point) from both intervention and control facilities, in each country. We will then conduct IDIs with a subset of providers (N = ∼ 40), facility leaders (N = ∼ 40), and mothers (N = ∼ 40) to explore pathways to intervention outcomes. Power analysis for sample size justification is described in the analysis section.

#### Recruitment

The study will first be introduced to the county/region, sub-county/district, and facility leadership, who will inform all providers who work in MCH units in the study facilities. The study’s field team will then approach individual providers to provide additional information and obtain written informed consent. Only providers who provide individual informed consent will be enrolled. They will be made aware that participation in the study is voluntary and will not affect their positions in any way. Providers in the selected facilities will be recruited by the field team and consented at the beginning of the study and then followed longitudinally for the three rounds of data collection. Women will be recruited at health facilities following discharge from the facilities and after postnatal care and in the immediate communities served by the study facilities. They will first be identified with the help of healthcare providers, community health volunteers, and a review of facility birth registers at the study sites. The study team will then screen them for eligibility, provide information about the study, and obtain individual informed consent if interested. Only women who provide written consent will be interviewed either at the facility, at their homes, or at a preferred location. Following surveys, all participants will be asked if they are willing to be contacted for follow-up IDIs; a subset of those who consent will be re-contacted for the IDIs. Participants for IDIs will be purposively sampled balancing for age, time/weeks since birth, and post-natal care attendance, to represent the range of experiences. All women will be consented prior to IDIs.

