### Study outcomes

#### Aim 1: The primary outcome of the study is PCMC to assess the effectiveness of the *CPIPE* intervention on PCMC.

PCMC will be measured with the PCMC scale developed and validated by our team in Kenya and Ghana [60–62]. The PCMC scale is a 30-item scale administered to perinatal women with 3 sub-scales for dignity and respect, communication and autonomy, and supportive care. Items for each scale are summed to create a score, which is standardized to range from 0 to 100, where higher scores indicate more person-centered care.

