### Analysis plan

#### Data quality assurance, initial analyses, and missing data

We will use Redcap to perform real-time checks for data quality assurance [69, 70]. We will use frequency tables and measures of central tendency and variability for continuous variables to characterize the sample overall and by randomization group. If the two groups differ significantly at baseline on one or more covariates, we will use methods based on the Rubin causal model (e.g., propensity scores, double-robust estimation) to obtain the desired effect estimates under the counterfactual assumption of balanced groups [71, 72]. We will address incomplete data with direct maximum likelihood (ML) and multiple imputation (MI) [73] because they make the relatively mild assumption that incomplete data arise from a conditionally missing-at-random (MAR) mechanism [74]. Auxiliary variables will be included to help meet the MAR assumption [75]. The proposed analyses will be conducted using STATA. All program code and results will be documented extensively and archived to enable future review, transparency, and results reproducibility.

##### Aim 1

We hypothesize that mothers in the *CPIPE* intervention group will have higher mean PCMC scores than mothers in the control group at 6 months (H1a) and 12 months (H1b) after baseline. To test hypotheses H1a-H1b, in primary analyses we will fit two-level linear mixed models (LMM) to the PCMC score. Each of these two models will include a fixed effect for the study arm with random intercepts for facility ID to account for the clustering of women within health facilities. Because we will compare *CPIPE* to control at 6 months and then repeat the same comparison at 12 months, alpha (α) will be set at 0.05/2 = 0.025 for each of these two planned comparisons. In secondary analyses for Aim 1, we will extend the LMMs for PCMC to include effects for age and SES and their interactions with the intervention group indicator to explore whether the *CPIPE* intervention differentially benefits younger and lower SES women. Sex as a Biological Variable is not applicable: all participants will be biological females.

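### Providers who know their arm, and whose care is being rated, help identify the women surveyed after randomisation, and the birth register is not fixed as the sampling frame

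*Protocol article*

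**What the plan says.** The Recruitment section of the protocol article describes how women enter the surveys: "They will first be identified with the help of healthcare providers, community health volunteers". The birth registers of the facilities are the third source named. Screening, information and consent by the study team come after that. On place and timing the section says: "Women will be recruited at health facilities following discharge from the facilities and after postnatal care and in the immediate communities". It gives no rule for combining the three sources and no split between the recruitment settings.

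Four other statements bear on this.

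- Study population: "Providers are the recipients of the intervention as well as potential beneficiaries".
- Data collection: the women are repeated cross-sections, and "data will be collected from 3 different groups of women at the 3 time points". Midline is 6 months after the intervention starts and endline is at 12 months.
- Study outcomes, Aim 1: "The PCMC scale is a 30-item scale administered to perinatal women with 3 sub-scales". The score reflects how women experienced the care given by the facility's staff.
- Analysis plan, Aim 1: "Each of these two models will include a fixed effect for the study arm with random intercepts for facility ID". No covariates enter the primary model. A propensity-score or double-robust adjustment is planned if the groups differ significantly at baseline, and likelihood or imputation methods are planned for incomplete data under a missing-at-random assumption.

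For Aim 3, which the article calls exploratory, it says: "We focus on the key outcome of receipt of timely post-natal care". That outcome is defined as postnatal care within 48 hours.

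**The concern.** In a cluster trial whose participants are found after allocation, randomisation protects the comparison only if finding them does not depend on arm. Here the people who help find them have, in one arm, been through months of training, refreshers and peer groups about the very behaviour that the women will be asked to rate. No bad faith is needed. Staff engaged with the project may think more readily of women whose births went well, or may be more active in referring women at all. Screening and consent by the study team come afterwards and cannot bring back women who were never put forward.

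The planned analyses do not reach this. The primary model compares the arms as sampled. The imbalance remedy is triggered by baseline differences, whereas selection that follows training appears only at midline or endline. Missing-at-random methods address incomplete records of sampled women, not women who were never sampled. Such selection could create a PCMC difference or hide one.

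A second, lesser issue concerns Aim 3. A woman with no postnatal care cannot enter through the stream recruited after postnatal care. That stream therefore favours attenders, and attendance is a precondition of the outcome in H3a and H3b.

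**Working it through.** **1. The plan's own figure for the primary outcome.** Inputs from the Aim 1 power analysis: 2,000 women per round, 40 facilities (50 each), ICC 0.16, alpha 0.025 (taken as two-sided), power 0.80.

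- Design effect = 1 + 49 × 0.16 = 8.84.
- Standard error of the standardised difference = √(4 × 8.84 / 2000) = 0.133.
- Minimum detectable difference = (2.241 + 0.842) × 0.133 = 0.41.

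This agrees with the stated d = 0.41. The figure is correct for an unselected sample, so the issue is bias and not sample size.

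**2. Shift in the primary comparison (assumed shares).** The article gives no selection rates, so everything in this step is illustrative and assumes no true effect and selection in one arm only.

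If a share s of one arm's women is steered, and these women score 1 SD above those they replace, the shift is s × 1 SD. The chance of a significant result is 1 − Φ(2.241 − shift/0.133) + Φ(−2.241 − shift/0.133).

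| Steered share | Shift (SD) | Shift / 0.41 | Type I error (nominal 0.025) |
|---|---|---|---|
| 10% | 0.10 | 24% | 0.07 |
| 20% | 0.20 | 49% | 0.23 |

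A second mechanism gives results of the same order. If one arm omits the fraction q of women with the worst experience and scores are normal, the mean rises by φ(z_q)/(1 − q). For q = 5%, 10% and 20% this is 0.11, 0.20 and 0.35 SD, with type I error of about 0.08, 0.22 and 0.65.

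**3. Aim 3 (assumed weights).** The stated minimum detectable differences are reproduced first. With ICC 0.039 the design effect is 1 + 49 × 0.039 = 2.911 and the effective size per arm is 1000/2.911 = 343.5. At 80% power and alpha 0.025 the detectable rise is 10.7 points from 24% and 8.3 points from 81%, as stated.

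Suppose women with timely care are w times as likely to be sampled as the others. The observed proportion is then pw/(pw + 1 − p).

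- *Equal oversampling, w = 2 in both arms, true 50% versus 60%.* Observed: 66.7% versus 75.0%. The raw difference falls from 10 to 8.3 points. The odds ratio does not move: (0.60/0.40)/(0.50/0.50) = 1.5 before, and (0.75/0.25)/(0.667/0.333) = 1.5 after.
- *Unequal oversampling, w = 1.5 in control and 2 in intervention, true 50% in both arms.* Observed: 60.0% versus 66.7%. This is a spurious 6.7 points, and the odds ratio becomes 2/1.5 = 1.33 when the truth is 1.

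The planned analysis is a generalised linear mixed model for a binary outcome. If its link is logit, which the article does not state, only oversampling of timely attenders that differs by arm distorts the effect. Attaching w to timely care itself is the extreme case, because the stream recruited after postnatal care also admits late attenders.

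**The case against.** The strongest reply is that help with identification is not selection. The sentence lists the birth register alongside providers and volunteers, and the study team does the screening and consenting. The text is compatible with staff merely locating women already found in the register. A journal article also condenses a fuller protocol, and field procedures commonly sit there. This stands in part: the article does not say that providers choose who is interviewed, and the lack of a quota or draw rule would not be a finding by itself. What the article does state, however, gives providers a part in first identifying participants and gives the register no priority over them. That is a design choice and not an omitted detail.

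The sizes above are assumed throughout. Control staff are being rated too, and equal steering in both arms would cancel. The endline comes 6 months after study-supported activity ends, so the incentive to steer may have faded by then. These points limit the claim to what can happen; they do not show that it will.

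A reader might infer that the H3 sample is selected on its own outcome. The documents do not support that. The outcome is care within 48 hours, whereas recruitment after postnatal care carries no such limit and eligibility runs to 12 weeks after birth, so late attenders can enter. Recruitment after discharge and in the community requires no postnatal care at all. Selection is partial and acts on a necessary condition of the outcome. Aim 3 is also exploratory and cannot carry the weight of the point.

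A reader might also conclude that recruitment at postnatal visits must stop. That goes too far. Relying wholly on home tracing could introduce its own selection, since Table 1 excludes women who live beyond a feasible distance when interviews take place in the community.

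**Conclusion.** The concern holds for the primary outcome and should be fixed. As written, the plan lets providers who know their arm help identify the women who will rate their care, at rounds that follow allocation, and no planned analysis corrects a resulting difference between arms. That providers know their arm is inferred from their receiving the training; the article describes no blinding.

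The size is unknown. One-sided steering of 10-20% with a 1 SD gap would use up about a quarter to a half of the detectable difference, but those shares are assumptions and nothing in the article supports a particular value. The conclusion is that arm-dependent selection is possible and uncorrected, not that the trial's result will be biased.

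For H3, over-representation of attenders raises the observed prevalence and can shrink a raw difference. It distorts an odds ratio only if the oversampling of timely attenders differs by arm.

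**What to change.** Make the birth register the sampling frame at baseline, midline and endline. At each round the study team lists all eligible births in the 12-week window at each facility and draws a random or consecutive sample before anyone is contacted. Providers and community health volunteers may then help locate women already drawn, but do not add names. Postnatal visits may remain a place to meet drawn women, but not a source of new ones. Report the numbers drawn, reached and refused by arm and round, so that differential non-location or refusal can be seen.

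The register review is already planned, and the sample size and minimum detectable differences do not change. The cost is real, though: more tracing of drawn women and somewhat slower recruitment, besides the change to the protocol and field instructions. Rounds already collected cannot be repaired by analysis. For those, report by arm how the women were identified, as far as it was recorded.
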